In our pilot work, Black and White patients with PD participated in a clinical phenotyping study, and the results showed no significant differences between the groups in sex, education, disease duration, Hoehn and Yahr stage, or Movement Disorder Society-Unified PD Rating Scale (MDS-UPDRS) part III Motor scores [10]. However, quantitative NIH Toolbox performance measures detected differences in gait and balance between Black and White participants with PD: gait speed (0.8±0.3 vs 1.1±0.2, *P*<.001), pegboard (41.4±15.6 vs 33.2±10.9, *P*=.04, and standing balance (32.7±13.1 vs 47±12, *P*<.01) [5]. In the nonmotor assessments, the Montreal Cognitive Assessment (23.4±3.1 vs 27±2.1, *P*<.005) and Symbol Digits Modalities Test (39.4±14.1 vs 49.6±9.1, *P*=.01) scores were worse in Black participants after correcting for education level. Hamilton Depression scale scores were worse in Black participants with PD compared with White participants (7±5.6 vs 4±3.5, *P*=.04), but other neuropsychiatric scales were similar between groups. The PD Quality of Life (PDQ-39) scores were higher (worse) in Black participants with worse ratings in participation in social roles and activities.

In summary, this pilot data showed differences in the motor examination, nonmotor features, and quality of life of Black patients with PD that warranted the current larger study. In our previous work and this protocol, race is self-identified by the patient as Black or White. Traditionally in the Chicago metropolitan area, this includes Black patients who are African, Afro-Caribbean, African American, or who report a mixture of races.

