### Objective

The overall objectives of this study are to perform comprehensive phenotyping, compare Black and White persons with PD, and investigate causes of racial disparities, including differences in clinical management and responsible genetic risk factors. The study is partnering with the ongoing Global PD Genetics Program (GP2) [19], which contributes samples and granular phenotypic data from the enrolled participants to enhance our understanding of the genetic architecture of PD in the Black population. The long-term goal of this application is to address the critical gap in knowledge of PD in this underserved population to improve diagnosis, optimize treatment, and plan for clinical trials. The central hypothesis is: PD is phenotypically and genetically different in Black versus White populations, and Black patients receive different and suboptimal clinical management. The research questions this study hopes to answer are as follows: (1) whether Black participants with PD have worse quantitative motor function and cognition, higher levels of depression and disability, and reduced quality of life compared with White participants with PD; (2) whether pharmacological, surgical, rehabilitation, mental health, and telehealth interventions differ by race with underuse of newer or more costly interventions in Black participants with PD; and (3) whether the contribution of genetic factors to PD risk and heterogeneity differs by race.

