### Outcome Measures

The primary outcome measures to characterize PD phenotypes include the NIH Toolbox Motor assessments (2-minute walk, 4-meter walk, balance test, pegboard test, and grip strength) [28]; the Montreal Cognitive Assessment (MoCA), Symbol Digit Modalities Test (SDMT), PROMIS Profile-29 Physical Function, Parkinson’s Disease Questionnaire-8 (PDQ-8), and the MDS-UPDRS. The primary outcome measures to assess PD clinical management include the proportion of participants with antiparkinsonian medications prescribed at the initial visit to the neurologist, the proportion of participants with initial treatment of depression, and the proportion of participants with PD surgical interventions. To characterize genetic risk variants in our sample, the frequencies of the 90 established common PD genetic risk variants based on published genome-wide association studies in a predominantly White population will initially be examined. The study team will also aggregate and summarize sequencing results from PD GENEration, including potential rare variants among 7 established PD genes. The proportion of LRRK2- and GBA-PD will be summarized based on either PD GENEration, which permits comprehensive detection of potential pathogenic alleles, or GP2 genotyping, which can detect many of the most common, recurrent pathogenic variants. Finally, exploratory genotype–phenotype analyses will determine whether established PD risk variants modify clinical manifestations in Black individuals.

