### Sample Size

The sample size was calculated for each primary outcome measure described above with 80% power and a 2-sided test to detect a similar effect size observed from our pilot data (Table 4). Bonferroni correction was applied to control the overall significance level at .05. The minimal sample size for these analyses requires 365 Black and 183 White participants to complete this aim. The data observed in 3 studies guided the sample size calculation for PD clinical management (White vs non-White or Black: 78% vs 62% for measure 1 [4], 92% vs 80% for measure 2 [56], and 10% vs 0.4% for measure 3 [57]). The sample size was calculated using 90% power and a 2-sided test for each primary measure. Bonferroni correction was applied to control the overall significance level at .05. With a 1:2 ratio, the largest sample size required among all 3 measures is 173 White patients with PD and 346 Black patients with PD. For the genetic studies, our sample size will permit exploratory analyses, and all data will be contributed to GP2 for fully-powered meta-analysis.

**Table 4 table4:** Pilot data effect sizes for sample size calculation.

Primary measures	White patients with PD^a^ (n=25), mean (SD)	Black patients with PD (n=25), mean (SD)
4-meter walk computed score	1.1 (0.2)	0.8 (0.3)
Balance *t* test score	47 (12)	32.7 (13.1)
Pegboard dominant score	33.2 (10.9)	41.4 (15.6)
MoCA^b^	27 (2)	23.3 (3.1)
SDMT^c^	49.6 (9.1)	39.4 (14.1)
PDQ-39^d^	12.8 (7.9)	22.5 (12.3)

^a^PD: Parkinson disease.

^b^MoCA: Montreal Cognitive Assessment.

^c^SDMT: Symbol Digit Modalities Test.

^d^PDQ-39: Parkinson’s Disease Questionnaire.

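### The 90% power claimed for the depression-treatment measure counts every PD participant as informative; if the 92% and 80% rates apply only to people with depression, it needs about 86.5% of the sample to have depression

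*Protocol article*

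**What the plan says.** Outcome Measures names three primary measures of clinical management. The second is "the proportion of participants with initial treatment of depression". No narrower denominator is given. Statistical Analysis compares the Black PD and White PD groups on each measure by chi-square or Fisher exact test.

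Sample Size takes its planning rates from three published studies, White versus non-White or Black: 78% vs 62% for measure 1, 92% vs 80% for measure 2 and 10% vs 0.4% for measure 3. It adds: "The sample size was calculated using 90% power and a 2-sided test for each primary measure". Bonferroni correction holds the overall level at .05, the ratio is 1:2, and the result is that "the largest sample size required among all 3 measures is 173 White patients with PD and 346 Black patients with PD".

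Study Setting and Design plans 200 White and 400 Black participants. Eligibility Criteria ask for a PD diagnosis, adulthood, self-identified race and consent, and do not mention depression. The article gives no depression prevalence and no allowance for participants without depression.

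**The concern.** The outcome definition, the planning rates and the derived number do not fit together.

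- **If 92% and 80% are rates over all PD participants**, at least 92% of White and 80% of Black participants would have to have been treated for depression. That is not credible in a sample with open eligibility.
- **If they are rates among people with depression**, then 173 and 346 count participants with depression. The article presents them as counts of patients with PD.

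On the second reading, one of three primary management measures has less power than stated unless nearly everyone has depression. Keeping everyone in the denominator does not help, because the proportion then mixes how common depression is with how often it is treated. The Objective section expects "higher levels of depression and disability" in Black participants and also expects underuse of interventions. In an all-participant proportion these two effects pull in opposite directions, so a real treatment gap could be understated.

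**Working it through.** **Inputs.** The rates, 90% power, two-sided testing and 1:2 ratio come from Sample Size. Alpha per measure is 0.05/3 = 0.01667, so z = 2.394; for 90% power z = 1.2816. Planned enrolment is 200/400 (Study Setting and Design). The share of participants with depression is not in the document and is assumed throughout.

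**Step 1: reproduce the plan's figure.** Pooled-variance formula without continuity correction, p1 = White, p2 = Black, p̄ = (p1 + 2·p2)/3:

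n(White) = [2.394·√(1.5·p̄(1−p̄)) + 1.2816·√(p1(1−p1) + p2(1−p2)/2)]² / (p1−p2)²

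- Measure 2: p̄ = 0.84. First term 2.394·√0.2016 = 1.0749. Second term 1.2816·√0.1536 = 0.5023. Then 1.5772²/0.0144 = 172.7, giving **173/346**, the stated figure.
- Measure 1: 166.5, giving 167/334.
- Measure 3: 94.8, giving 95/190.

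Measure 2 is the largest and matches exactly. No share with depression enters the calculation, so all 173 and 346 are counted as informative.

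**Step 2: power if only participants with depression count.** With share f in both groups, the White group contributes 200f and the Black group 400f:

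power = Φ[(0.12·√(200f) − 1.0749)/0.3919]

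At f = 0.40 this is 0.12·√80 = 1.0733, so Φ(−0.004) = 0.50.

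| Assumed share | Informative at 200/400 | Power at 200/400 | Power at 173/346 |
|---|---|---|---|
| 30% | 60/120 | 36% | 30% |
| 40% | 80/160 | 50% | 42% |
| 50% | 100/200 | 63% | 54% |
| 60% | 120/240 | 73% | 65% |
| 100% | 200/400 | 94% | 90% |

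For 90% power at 200/400 the share must be about 173/200 = 86.5%. Fisher exact power at 200/400 agrees closely: 33%, 48% and 63% at shares of 30%, 40% and 50%. Unequal shares do not rescue it: 30% White with 50% Black gives 39%, and 50% with 70% gives 67%.

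**Step 3: power with the literal all-participant denominator.** The proportions become 0.92f and 0.80f over the full 200 and 400.

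- f = 30%: 27.6% vs 24.0%, power 8%.
- f = 40%: 36.8% vs 32.0%, power 11%.
- f = 50%: 46.0% vs 40.0%, power 16%.

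**Step 4: unequal prevalence with that denominator.** The contrast is zero when 0.92·f(White) = 0.80·f(Black), that is when the Black share is 0.92/0.80 = 1.15 times the White share. For example, 30% and 34.5% both give 27.6%. A larger ratio reverses the sign.

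**The case against.** There is no arithmetic slip: 173/346 follows exactly from the stated inputs. The question is which population those inputs describe, and the article does not say that 92% and 80% are rates among people with depression. This stands, and it makes the power loss conditional. It does not rescue the stated power, because the alternative reading requires near-universal treatment for depression.

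A reader might take the pilot result, "Hamilton Depression scale scores were worse in Black participants with PD compared with White participants" (means 7 and 4), as proof that few participants have depression. It is not. Those scores show current symptoms in a small pilot, whereas measure 2 concerns initial treatment, which may lie in the past. A successfully treated patient can score low. The point therefore does not rest on these scores.

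A reader might also infer that the prevalence and treatment effects will cancel. The article gives directions, not sizes, and the 30%/34.5% pair was chosen to make the contrast zero. Only the direction of the distortion is supported.

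The full protocol or an appendix may define the denominator. A missing operational detail would be no criticism of an article. Here, however, the article itself states an outcome, rates, comparison groups and a power that do not agree.

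Finally, 173/346 does not set enrolment. The phenotyping aim needs 183/365, and 200/400 is planned. That is correct, but the slack covers shares only down to about 86.5%.

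**Conclusion.** The point holds in conditional form. It is certain that 173/346 comes from measure 2 alone and counts every PD participant as informative, and that neither eligibility nor the outcome definition restricts the sample to people with depression. It is inferred that the 92% and 80% rates apply to people with depression, since the source is not at hand. It is assumed what share of participants that is.

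On that basis the 90% claim for measure 2 holds only at a share of about 86.5% or more. Across shares of 30% to 60%, power is about 36% to 73%. The all-participant version has still less power and is open to distortion by differing prevalence.

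The documents do not support a flat statement that the study is too small. Measures 1 and 3 are unaffected: even at 173/346 their power is about 91% and 99%.

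**What to change.** - Define measure 2 as the proportion treated among participants with depression. Where possible, identify them by criteria that do not depend only on a previously recorded diagnosis. If access to care differs by race, as the Background describes, a diagnosis-based denominator could drop under-diagnosed Black participants and hide a disparity.
- Report the all-participant proportion as a secondary measure.
- State in Sample Size that 173/346 refers to participants with depression. Replace the 90% claim for measure 2 with power at 200/400 over a stated range of shares, labelled as assumptions.
- Keep the 90% claim for measure 1 (167/334) and measure 3 (95/190).

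**Cost.** One outcome definition and one power statement change, and the stated power for measure 2 becomes less favourable. Some bias from differential diagnosis may remain and should be noted as a limitation. No extra patients are needed.

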### Data Collection and Monitoring

The co-principal investigators (DH and LS), core administrative, and coordinating personnel meet weekly to identify potential issues with consent or assessment procedures, manage any reported adverse events, and monitor the sites’ progress. The REDCap database created to house the data is audited weekly to ensure fidelity. All study data are directly entered into the REDCap database in real time unless internet connectivity is an issue at the site.

### Statistical Analysis

Each primary outcome measure will be compared between Black and White patients with PD. Bonferroni correction will be applied. The primary outcome measures are a 4-meter walk computed score, Balance test *t* score, Pegboard dominant *t* score, MDS-UPDRS motor score [26], MoCA [33], SDMT [58], PROMIS Profile-29 Physical Function, and PDQ-8 [46]. For significant measures, linear regression analysis will be performed to examine further the difference between the 2 groups with adjustment for age, sex, and disease duration. The interaction effects of race with these 3 variables will be explored. Regression analysis for cognitive measures will adjust for depression and anxiety scales in addition to these demographics. Regression will also be adjusted for comorbidities using the Cumulative Illness Rating Scale-Geriatrics score. The study site effect will be controlled as a random effect in the model. All analyses will be done using SAS (version 9.4).

For the PD management analysis, each primary outcome measure will be compared between Black PD and White PD groups using the chi-square test or Fisher exact test. Bonferroni correction will be applied. A hierarchical logistic regression analysis will assess the determinants of racial disparities in management. Besides race, age, sex, and education, income, symptom severity, and comorbidities will be included in the model. The interaction effect of race with those variables will be explored. The study site effect will be controlled as a random effect in the model. Secondary analyses will investigate differences between White PD and Black PD groups in other clinical management measures, including telehealth, participation in clinical trials, and rehabilitation therapy.

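### Single-step Bonferroni is valid here, but Holm's procedure would give equal or greater power at the same family-wise .05; the size of the gain depends on how many primary measures truly differ

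*Protocol article*

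**What the plan says.** The Statistical Analysis section sets the multiplicity method for the phenotype measures: "Each primary outcome measure will be compared between Black and White patients with PD. Bonferroni correction will be applied". It then lists eight measures: 4-meter walk, balance, pegboard, MDS-UPDRS motor, MoCA, SDMT, PROMIS Physical Function and PDQ-8. The three management proportions also get a Bonferroni correction. No step-down procedure or ordering is described.

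The Sample Size section uses the same method: "Bonferroni correction was applied to control the overall significance level at .05". Each Aim 1 measure is sized separately: "The sample size was calculated for each primary outcome measure described above with 80% power and a 2-sided test". Aim 2 is sized at 90% power per measure.

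The corrected Aim 1 result has a further use: "For significant measures, linear regression analysis will be performed to examine further the difference between the 2 groups". The Aim 2 logistic regression carries no such condition.

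The Outcome Measures section also counts the 2-minute walk and grip strength as primary, which makes ten measures rather than eight.

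**The concern.** Single-step Bonferroni tests every Aim 1 measure at .05/8 = .00625, however clearly the others are rejected. Holm tests the smallest p-value at .05/8, the next at .05/7, and so on, stopping at the first failure. It needs no extra data, no ordering and no assumption about correlation. When several measures are clearly different, Bonferroni leaves allowed error unused and gives up power on the borderline ones.

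That pattern is plausible here. The pilot effects in Table 4 are large. The Background reports no significant pilot difference in MDS-UPDRS part III, and no pilot figure is given for PROMIS Physical Function. Those two measures are the likely borderline cases. A measure missed in Aim 1 also goes without its planned adjusted comparison.

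**Working it through.** **Inputs from the article.** Family-wise level .05, two-sided; eight Aim 1 measures (Statistical Analysis); 200 White and 400 Black planned (Study Setting and Design); means and SDs from Table 4 ("Pilot data effect sizes for sample size calculation").

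**Assumptions.** Effects for MDS-UPDRS motor and PROMIS Physical Function (0.25 SD, then 0.324 SD); the pilot PDQ-39 effect stands in for PDQ-8; correlation between measures of 0, 0.3 or 0.5.

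**Pilot effects.** d = mean difference / √[(SD₁² + SD₂²)/2]. The smallest is pegboard: 8.2 / √[(15.6² + 10.9²)/2] = 8.2/13.46 = 0.61. The others are SDMT 0.86, PDQ-39 0.94, balance 1.14, walk 1.18 and MoCA 1.42.

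**The plan's own figures.**
- Aim 2 reproduces. For 92% vs 80%, two-sided .05/3, 90% power and a 1:2 ratio, the weighted mean proportion is 0.84. Then n(White) = [2.394·√(0.84·0.16·1.5) + 1.282·√(0.92·0.08 + 0.80·0.20/2)]² / 0.12² = 172.8, so 173 White and 346 Black, as stated.
- Aim 1 (183/365) does not follow from Table 4. Its most demanding measure, pegboard, needs 52/104 at .00625 and 80% power. With √(183·365/548) = 11.04, the stated size corresponds to d = (2.734 + 0.842)/11.04 = 0.324. It may rest on a measure that Table 4 omits.

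**Power at 200/400.** Power = Φ(d·√(200·400/600) − z), where the square root is 11.547 and z is the two-sided critical value.

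| Level | z | d = 0.25 | d = 0.324 |
|---|---|---|---|
| .05/8 = .00625 | 2.734 | 0.561 | 0.843 |
| .05/5 = .01 | 2.576 | 0.622 | 0.878 |
| .05/2 = .025 | 2.241 | 0.741 | 0.933 |
| .05 | 1.960 | 0.823 | 0.963 |

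**Holm power.** At pilot-size effects the six Table 4 measures are rejected almost surely, so two measures remain. The first faces .025. The last faces .05, and only if the first is rejected. With independent measures:
- Both at 0.25 SD: 0.741 + (0.823 − 0.741)·0.741 = 0.80, against 0.56 under Bonferroni.
- One at 0.25 SD, the other null: 0.741 + 0.082·0.025 = 0.74, against 0.56.
- Both at 0.324 SD: 0.933 + 0.030·0.933 = 0.96, against 0.84.
- One at 0.25 SD, three others truly different, four null: the test is at about .05/5, giving 0.62, against 0.56.
- One at 0.25 SD, no other difference: 0.56 under both.

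Simulation of eight z-tests (200,000 runs, correlations 0, 0.3 and 0.5) gives the same results to within about one percentage point.

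**Error rate.** With six pilot-size effects and two true nulls, the simulated family-wise error is about 0.012 under Bonferroni and 0.046 to 0.049 under Holm. Both respect .05.

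**Aim 2.** At 173/346, with measures taken as independent, power for measures 1 and 2 rises from 0.91 to 0.96 each. The chance that all three are significant rises from 0.83 to 0.93.

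**The case against.** The strongest reply is that nothing is wrong. Bonferroni is valid, prespecified and consistent between sizing and analysis. Because each measure was powered separately under it, the study has already paid for the conservatism in sample size. This stands: the point is about efficiency. A reader might infer that the plan is in error or underpowered because of Bonferroni, and the documents do not support that. At pilot-size effects the six Table 4 measures have power of about 1.00 under either method. At 0.324 SD, Bonferroni already gives 84% with 200/400.

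A second reply concerns the size of the gain. The 24-point rise needs all eight measures to differ and two of them to differ by 0.25 SD, a value the article does not give. This also stands. At 0.25 SD the gain runs from nil to about 24 points, depending on how many other measures differ.

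Two other inferences go too far. One is that the remaining measures would be tested at .05: with two left, the first faces .025. The other is that Holm would secure an adjusted estimate for every measure. It would not, because an unadjusted test would still decide which Aim 1 measures go on to regression. That rule is a separate issue, and it does not apply to the Aim 2 regression.

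There is also a real trade-off in reporting. A measure significant under Holm can have a Bonferroni interval that includes zero.

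**Conclusion.** The point holds as an optional improvement. Holm is never less powerful than the stated method at the same family-wise .05 bound, and the sizing is unaffected because Holm's first step also uses .05 divided by the number of measures. For a borderline Aim 1 measure at an assumed 0.25 SD, power at 200/400 goes from 56% to 80% in the most favourable case shown, to 74% with one true null, to 62% with four, and stays at 56% if it is the only true difference. If both measures without Table 4 effects are assumed to differ by 0.324 SD, each goes from 84% to 96%. These figures rest on a family of eight, on the assumed effects for those two measures and, except where stated otherwise, on pilot-size effects elsewhere.

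**What to change.** In Statistical Analysis, replace the Bonferroni sentence for each aim with: Holm's step-down procedure will control the family-wise error at .05 within each aim. Apply it to one fixed list of primary measures. Outcome Measures and Statistical Analysis currently give ten and eight for Aim 1, and Holm needs a defined family just as Bonferroni does. Keep Bonferroni in Sample Size as the conservative planning basis.

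The cost is one sentence per aim and no participants. With 131 enrolled at manuscript submission out of 600 planned, the change can be prespecified before the groups are compared. Intervals that match Holm are less simple, so report intervals labelled as unadjusted or Bonferroni, and say that they may not agree with the Holm decision. The rule that sends only significant Aim 1 measures to regression should be considered separately.

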**Methods:**

This is an observational, prospective, multicenter, case-case design study. Other aims will investigate the management of PD in Black individuals and the presence of shared or unique genetic risk factors among the Black PD population. A total of 400 Black and 200 White participants with PD will be recruited. Data will be collected at 7 US sites and entered into a Research Electronic Data Capture database. Linear multivariate regression analysis will be used, except for comparing PD management, which will be analyzed using the chi-square test or Fisher exact test. Bonferroni correction will be applied. This protocol also describes plans for educational programming for clinicians and patients at the end of the study in partnership with national PD organizations.

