### Recruitment and Screening Strategies

Recruitment will occur in the outpatient movement disorder clinics at the 7 study sites. Treatment clinicians or study coordinators will approach potential participants to discuss participation. Potential participants will be identified by prescreening medical records or by referral to the treating provider. Each White participant was initially matched to be within 5 years of age of the mean age of every 2 Black participants enrolled at the same site. Each time 2 Black participants were enrolled at a site, the study statistician would contact the site with the age range of the next White participant. Part-way through the study, propensity matching replaced this manual process. Potential participants will be interviewed to determine if they meet the eligibility criteria for enrollment.

Black patients with PD have been underrepresented in clinical research [22]. Therefore, study planning includes targeted strategies to facilitate recruitment and foster participant satisfaction with research participation. An advisory board of 6 individuals comprised of Black individuals with PD and family members of affected individuals assists in developing outreach strategies and providing feedback on their study visit experience, with protocol modifications as needed. The patient advisory board members will have participated in the study at 1 of the study sites. Educational strategies include initiatives for both study participants and study staff. A brief video and flip charts with culturally appropriate information are used to improve understanding of participation in research, including the informed consent process [23]. Participation of Black study coordinators is encouraged to foster rapport and cultural sensitivity. Teaching cross-cultural sensitivity is part of the prestudy and annual activities for all site investigators and coordinators [24]. Barriers to recruitment and enrollment will be explored, with each enrolled participant completing a Participations in Clinical Trials Questionnaire that includes a question on barriers to research participation [25]. During quarterly Steering Committee meetings with all site investigators, recent publications on minority recruitment and research are reviewed with the study author.

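### Adjusted race comparisons in Aim 1 are planned only for measures that first pass a Bonferroni test with no stated covariates, and the governing result is not named

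*Protocol article*

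**What the plan says.** In the Statistical Analysis section, Aim 1 has two steps.

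- Step 1: "Each primary outcome measure will be compared between Black and White patients with PD", with Bonferroni correction. Neither the test nor any covariate is named. Eight measures are listed, beginning "The primary outcome measures are a 4-meter walk computed score, Balance test *t* score, Pegboard dominant *t* score, MDS-UPDRS motor score" and continuing with MoCA, SDMT, PROMIS Physical Function and PDQ-8.
- Step 2: "For significant measures, linear regression analysis will be performed to examine further the difference between the 2 groups". The covariates named for this model are sex, age and disease duration. The section adds depression and anxiety for the cognitive measures, site as a random effect, and comorbidity: "Regression will also be adjusted for comorbidities using the Cumulative Illness Rating Scale-Geriatrics score".

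The abstract's Methods paragraph has no such condition: "Linear multivariate regression analysis will be used, except for comparing PD management". The Aim 2 logistic regression, in the same Statistical Analysis section, is not conditional on a first test either.

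Under Recruitment and Screening Strategies, White participants were at first matched on age within site. Then: "Part-way through the study, propensity matching replaced this manual process". The article does not list the propensity covariates.

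**The concern.** The authors judge age, sex, disease duration, comorbidity and site worth adjusting for, but a comparison that states none of them decides whether the adjustment is done. Three things follow.

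1. A measure whose race difference is masked by an imbalance, or is too small for the first test, gets no adjusted estimate. MDS-UPDRS motor is the plausible candidate: it is a primary measure, and the pilot described in the Introduction found no significant difference in it.
2. The adjusted estimates that are reported form a subset selected on the crude p value. The Genetic Analysis section then draws further modifier outcomes from the Aim 1 results, so the selection carries forward.
3. When a measure passes step 1 and its difference shrinks or disappears after adjustment, the text does not say which result is the study's conclusion.

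**Working it through.** **The passages side by side**

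| Place | Adjusted model fitted for |
|---|---|
| Abstract, Methods | all outcomes except management |
| Statistical Analysis, Aim 1 | only measures significant at step 1 |
| Statistical Analysis, Aim 2 | no significance condition |

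The first two rows cannot both describe the plan. The point rests on this order of analysis and not on any figure stated in the article.

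**How much the condition could matter**

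Inputs from the article: 200 White and 400 Black participants (Study Setting and Design), overall alpha .05 with Bonferroni correction (Sample Size), eight measures (Statistical Analysis). Per-test alpha = .05/8 = .00625, two-sided. Degrees of freedom = 598, critical t = 2.744.

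Assumed, because the article gives no values: the adjusted difference and the amount by which imbalance offsets it. A difference of 0.33 SD is a reasonable scale. The stated Aim 1 minimum of 183 and 365 detects, at 80% power, (2.734 + 0.842) × √(1/183 + 1/365) = 3.576 × 0.0906 = 0.32 SD.

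Noncentrality = d / √(1/200 + 1/400) = d × 11.547. Power comes from the noncentral t.

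| Offset (SD) | Crude d | Noncentrality | Passes step 1 |
|---|---|---|---|
| 0 | 0.33 | 3.81 | 86% |
| 0.05 | 0.28 | 3.23 | 69% |
| 0.10 | 0.23 | 2.66 | 47% |
| 0.15 | 0.18 | 2.08 | 25% |

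The number of measures hardly changes this. With 6 measures (the Table 4 count) or 10 (the Outcome Measures count), the last row becomes 29% or 23%.

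**Without any confounding.** At d = 0.30 the crude test has 76% power. If covariates explain 10%, 20% or 30% of the variance, the effective d is 0.30/√(1 − R²) = 0.316, 0.335 or 0.359, and power is 82%, 87% or 92%. This is a loss of efficiency, not a bias.

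**Simulation with one confounder** (3,000 replicates; assumed slope 0.4 SD per SD)

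| Adjusted race effect | Confounder imbalance | Crude significant | Adjusted significant | Both |
|---|---|---|---|---|
| 0.30 SD | none | 76% | 84% | 75% |
| 0.30 SD | 0.25 SD, masking | 32% | 84% | 32% |
| 0.30 SD | 0.50 SD, masking | 5% | 82% | 5% |
| 0 | 0.50 SD | 33% | 0.6% | 0.2% |

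Rows 2 and 3 show the cost of the condition. Row 4 shows why the governing result must be named: a crude finding produced by imbalance nearly always disappears on adjustment, but the plan does not say that the adjusted result then stands.

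**Limit of the effect.** The smallest Table 4 effect is the pegboard: pooled SD = √((10.9² + 15.6²)/2) = 13.46 and d = 8.2/13.46 = 0.61. Its noncentrality is 7.03 against a critical value of 2.744, so crude power exceeds 99.9%. The other five effects are larger. The condition affects only differences well below the pilot's, or masked ones.

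**The case against.** Four stronger readings are tempting, and the article does not support them.

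- *The crude test decides every Aim 1 conclusion.* It does not. It alone settles the measures that fail; those that pass go on to the adjusted model. What is missing is a statement of which result governs.
- *Failing step 1 will be reported as no difference.* The article nowhere says so. It only omits an adjusted analysis for those measures.
- *The first comparison is confounded.* This is not shown. Same-site age matching, and later propensity matching, balance part of the covariate set, and the pilot found no significant difference in sex or disease duration. That is weak evidence at 25 per group, but it points to no imbalance. Balance and pegboard are analysed as T scores, and Table 1 refers to age and gender norms, so step 1 may already reflect age and sex there. That step 1 is unadjusted is itself an inference: the test is unnamed and covariates appear only in step 2.
- *The crude difference should be demoted to description.* Research question 1 asks whether Black participants have worse function, cognition and quality of life, and a total difference is a legitimate answer. Disease duration and comorbidity may lie on the pathway from the unequal access that the Introduction describes, so a fully adjusted coefficient answers a different question.

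It is also fair to say that an abstract is condensed, and that propensity covariates may be listed in the full protocol. None of this justifies making adjustment depend on a significance test. The initial matching covered age and site only, and the article itself considers sex, duration and comorbidity necessary in the model.

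**Conclusion.** The point holds in this form: the article fixes a rule under which Aim 1 measures that miss a Bonferroni threshold in a comparison with no stated covariates receive no adjusted estimate. The rule conflicts with the abstract, and the governing result is left open for measures that pass. The size is conditional. An assumed 0.33 SD difference falls from about 86% to about 25% probability of reaching the adjusted model if imbalance offsets it by 0.15 SD, and to 69% if the offset is 0.05 SD. The article supplies neither figure. Effects of the size in Table 4 are unaffected. This is a should-fix.

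**What to change.** - In Statistical Analysis, strike the opening condition that limits the regression to significant measures. Fit the model already specified to all eight primary measures: age, sex, disease duration, CIRS-G and random site, plus depression and anxiety for MoCA and SDMT.
- Report crude and adjusted race differences with confidence intervals side by side for every measure.
- State, before any race comparison is seen, which of the two carries the Bonferroni-controlled claim. The adjusted race coefficient would match the abstract. If the crude difference is chosen, say that it is the total disparity and treat the adjusted one as explanatory.
- Make the abstract and the Statistical Analysis section agree.

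The cost is a few sentences and at most eight models in place of a subset, with no new data or enrolment. At submission 131 of the planned 600 participants had been enrolled. The one real decision is the governing estimate, because duration and comorbidity may partly mediate the disparity.
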